#### Sample size {14}

The sample size was projected with a change in ApoB as the main outcome variable between HIFT1 and HIFT3. Power calculations (IBM SPSS v25 Armond, NY) assumed a 1:1 equal allocation between HIFT1 and HIFT3. The baseline mean and standard deviations from a previous study [97] and pilot studies for ApoB were ~ 129 ± 25 mg/dL in sedentary adults with elevated cardiometabolic risk. Collectively, using these data, we consider a 15% reduction in ApoB to be clinically meaningful within the HIFT3 group [98]. Assuming a power of 0.90, *α* = 0.05, and an effect size of *d* = 0.80, a paired samples one-tailed *t*-test sample size calculation revealed a sample size of 60 subjects (20 per group) will establish the superiority of HIFT3 versus HIFT1 for pre- to post-differences in the primary outcome ApoB. With an estimated 5% dropout rate, we will recruit 22 subjects/group to obtain the necessary sample size of 60. Therefore, a total of 60 men and women who meet the previously stated inclusion criteria will be recruited and randomized post-baseline assessments into one of the three intervention groups. Data will be collected in cohorts of 12, randomized into intervention groups. This will continue until 20 participants per intervention group have completed the study. This will accommodate dropout within cohorts.

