## Statistical methods

### Statistical methods for primary and secondary outcomes {20a}

Only data from participants who complete ≥ 80% of total exercise intervention and with no noticeable change in eating (statistically different energy consumption and macronutrient distribution) and physical activity habits will be included [97, 99, 100]. All data will be analyzed using the Statistical Package for the Social Sciences (IBM SPSS v25, Armond, NY). Descriptive data if normal will be presented as mean ± SD, or median and interquartile range if not normal; the significance level of all comparative data will be set as *p* ≤ .05, and normality will be assessed using a Kolmogorov-Smirnov test. If normality exists, parametric tests will be used, if normality does not exist, non-parametric tests will be used. Effect sizes (ES) and confidence intervals (CI) will be calculated on the results of all dependent variables. Paired *t*-tests will be used to evaluate the significant differences between pre- and post-measures of both primary and secondary physiological outcomes within each group. A one-way ANOVA will be used to compare the primary and secondary outcomes pre-post mean change between the three groups. When indicated by a significant *F* value, post hoc analysis will be determined using the Bonferroni adjustment for multiple comparisons. The median, mode, and interquartile ranges of the IFIS and PACES data will be calculated for each of the three groups. Should missing data in outcomes occur, a linear-mixed model will be conducted instead of ANOVA as this test accounts for missing data.

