### Methods in analysis to handle protocol non-adherence and any statistical methods to handle missing data {20c}

Participant adherence will be determined by completion of ≥ 80% of total exercise intervention and no noticeable change in eating and physical activity habits, assessed by the Block questionnaires. Should non-adherence occur, outcome variables will be tested using two analysis sets: the intention-to-treat set, considering all randomized participant data regardless of intervention adherence, and the per-protocol set, considering only data from participants who complete ≥ 80% of the total exercise intervention. Analyses will be performed to examine the effect of the different strategies on the conclusions. If intention-to-treat analyses are determined appropriate, reasons for withdrawal will be reported and compared qualitatively. If missing outcome variables occur, imputation of missing data will be considered. To account for missing data, a linear mixed-model analysis will be used to determine if there are differences in the primary outcome variable of ApoB.

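### Section {20a} restricts the analysis on post-randomisation adherence, diet and activity, contradicts the intention-to-treat text in {20c}, and leaves the primary analysis set undefined

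*Protocol article*

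**What the plan says.** Section {20a}, on methods for the primary and secondary outcomes, opens with the analysis population: "Only data from participants who complete ≥ 80% of total exercise intervention". The same sentence adds a second condition, that only those "with no noticeable change in eating (statistically different energy consumption and macronutrient distribution) and physical activity habits will be included". Neither condition is qualified, and the section does not refer to any other analysis set.

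Section {20c}, on non-adherence and missing data, defines adherence by the 80% rule together with unchanged diet and activity. It then says "Should non-adherence occur, outcome variables will be tested using two analysis sets". One is "the intention-to-treat set, considering all randomized participant data regardless of intervention adherence". The other is "the per-protocol set, considering only data from participants who complete" at least 80% of the training, with no diet or activity condition. The section promises to examine how the choice of strategy affects the conclusions, and continues: "If intention-to-treat analyses are determined appropriate, reasons for withdrawal will be reported and compared qualitatively". Neither set is called primary.

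Section {16a} places randomisation after baseline testing and the adaptive period, so before the 12 training weeks. Section {11d} has diet and activity questionnaires before, midway through and after the study. Section {14} recruits in cohorts and states: "This will continue until 20 participants per intervention group have completed the study". Section {15} repeats that target.

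**The concern.** The randomised factor is how many sessions a week a person is asked to do. Completing 80% of those sessions, taking up other exercise and changing diet all happen afterwards, and each could plausibly be influenced by that factor. A comparison limited to people who satisfy all three conditions is between selected subsets of the arms. Differences in ApoB change could then reflect who was kept and not the dose.

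The conflict between the two sections matters as much. One excludes people whom the other says will be analysed, and nothing says which result carries the conclusion. That choice could be made after the results are known.

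The diet rule adds a further judgement. It is worded as a significance test, yet it is used to decide whether one individual stays in.

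**Working it through.** **1. The sets side by side.** Three hypothetical participants, all with post-test data:

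| Participant | {20a} population | {20c} intention-to-treat | {20c} per-protocol |
|---|---|---|---|
| 90% of training, habits unchanged | in | in | in |
| 90% of training, diet changed | out | in | in |
| 70% of training, habits unchanged | out | in | out |

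The three sets all differ. The second participant is non-adherent by the definition in {20c} but still belongs to its per-protocol set. The {20a} population therefore matches neither set in {20c}.

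**2. The diet criterion.** Each participant supplies three questionnaires at three different times: one baseline, one midway, one final. A change from baseline for one person is a single difference, with no replicate at either time from which to estimate that person's own reporting error. No within-person significance test can be built on that without an outside error estimate, and the document gives none. A test across a group is possible but cannot identify which individual to exclude.

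**3. The plan's own allowance for losses.** Section {14} allows 5% dropout: 20 / (1 − 0.05) = 21.05, rounded up to 22 per group, as stated. No allowance is stated for exclusions under {20a}. If those removed 10%, 20%, 30% or 40% (assumed; the document gives no rate), keeping 20 analysed would need 20/0.9, 20/0.8, 20/0.7 or 20/0.6, that is 23, 25, 29 or 34 per group. Whether this bites depends on what completing the study means in {14} and {15}, which is not defined.

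**4. What the 80% rule does by arm (illustration).** Assume completion is counted in sessions. Planned sessions are 12 × 1 = 12, 12 × 2 = 24 and 12 × 3 = 36. The minimum is 0.8 × 12 = 9.6, so 10; 0.8 × 24 = 19.2, so 20; 0.8 × 36 = 28.8, so 29. With X ~ Binomial(N, p), the share excluded is P(X < minimum). For the same assumed p in every arm and independent sessions:

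| Assumed p | HIFT1 | HIFT2 | HIFT3 |
|---|---|---|---|
| 0.80 | 44.2% | 54.0% | 43.4% |
| 0.85 | 26.4% | 28.7% | 16.2% |
| 0.90 | 11.1% | 8.5% | 2.4% |
| 0.95 | 2.0% | 0.6% | 0.0% |

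Identical attendance behaviour can still give unequal exclusion, because the rule is applied to different numbers of sessions.

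**5. Whether unequal exclusion can create a difference (illustration).** Suppose there is no true effect, and a latent adherence tendency has correlation r with the outcome. If the lowest fraction e is excluded, the mean outcome of those kept shifts by r × φ(c)/(1 − e) SD, where c is the normal quantile at e.
- e = 0.05: 0.1031/0.95 = 0.109.
- e = 0.25: 0.3178/0.75 = 0.424.
- Excluding 5% of HIFT1 and 25% of HIFT3 gives r × 0.315: 0.06 SD at r = 0.2 and 0.16 SD at r = 0.5.
- If the SD of change were 25 mg/dL (the document gives 25 only for baseline), that is 1.6 to 3.9 mg/dL.
- Swapping the two rates reverses the sign. Equal rates give zero.

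**The case against.** Section {20c} mitigates part of this. It commits to both sets if non-adherence occurs, and to comparing their conclusions. Without non-adherence the two sets coincide on adherence, so that first condition does little harm. The later clause about intention-to-treat being appropriate governs, grammatically, only the reporting of withdrawal reasons. A reader might infer that the intention-to-treat analysis may be skipped; the text does not say so, though the wording does imply that it is optional. The trial is also declared exploratory, {11d} prohibits added diet and exercise interventions (so a diet or activity condition is legitimate in a per-protocol set), and {13} attaches no attendance condition to post-testing. All of this stands. None of it removes the unqualified restriction in {20a} or says which set is primary. Nor is this detail left to a fuller document: the article fixes incompatible populations, and {31c} calls it the full protocol.

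Four stronger readings are tempting and are not supported.

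- **That the rule favours the most demanding arm.** This needs worse adherence in HIFT3. No rate by arm is given, and under equal session attendance HIFT3 loses the fewest. That model is itself weak: with sessions on three weekdays, a one-session participant may be able to use another day, whereas a three-session participant needs all three.
- **That the effect would be overstated by one third.** If 25% of HIFT3 failed the rule and gained nothing, a 15% fall would become 0.75 × 15% = 11.25%, and 15/11.25 = 1.33. This is only 1/0.75, the assumption restated. It dilutes one arm alone, and it gives no benefit to someone with 28 of 36 sessions, who fails the rule yet has done more than HIFT2's full 24.
- **That fewer than 20 per group will be analysed.** If completing the study already includes the 80% rule, that rule does not reduce the number. The fault is the undefined term.
- **That enjoyment scores will be inflated.** It is plausible that people who disliked their sessions attend less, but the document offers nothing to establish or size it.

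**Conclusion.** The point holds as a wrong rule and an internal contradiction. Followed as written, {20a} selects the analysis population on events after randomisation, so the dose comparison is no longer a randomised one. Section {20c} specifies a different approach, and the primary set is undetermined. These conclusions rest on the text alone. The direction and size of any bias cannot be derived from the document: the exclusion rates by arm assume a common attendance probability and independent sessions, and the shift of 0.06 to 0.16 SD assumes its own exclusion rates and correlations. Neither is a forecast. Even in an exploratory trial this should be settled before outcomes are analysed, because the remedy is cheap and the choice would otherwise be open once results are known.

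**What to change.** - In {20a}, delete the restriction that begins "Only data from participants who complete".
- Make all randomised participants, analysed in the arm to which they were allocated, the unconditional primary set. The linear mixed model already planned for missing outcomes can serve it.
- State that post-testing applies regardless of attendance.
- Keep one per-protocol set as supportive, defined identically in {20a} and {20c}. If diet or activity stays in it, use a threshold fixed in advance and not a significance test.
- Report diet and activity changes by arm.
- In {20c}, remove both conditional phrases: the one making the two sets depend on non-adherence, and the one making intention-to-treat depend on being judged appropriate.
- In {14} and {15}, say whether the 20 per group are participants post-tested or participants meeting the per-protocol definition.

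The cost is protocol wording, plus existing post-test visits for any non-adherers who would not otherwise have attended. The downside is an estimate that may be somewhat diluted relative to full adherence; the per-protocol analysis remains available to show that.

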#### Relevant concomitant care permitted or prohibited during the trial {11d}

To isolate the effects of the intervention alone, all participants will complete a physical activity and diet questionnaire [70, 71] prior to the start of the study. Participants will be asked to maintain the same behaviors throughout the study, then fill out the questionnaires midway and after the study to verify. Participants will be informed that any additional dietary and exercise interventions will be prohibited throughout the study.

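### The diet-stability rule rests on statistical significance: it cannot be applied to one participant, and in a group of 20 per arm a non-significant test does not show that diet was stable

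*Protocol article*

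**What the plan says.** Three sections of the protocol article bear on this.

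- **Statistical methods for primary and secondary outcomes {20a}** restricts the analysis to participants who complete at least 80% of the intervention and who show "no noticeable change in eating (statistically different energy consumption and macronutrient distribution) and physical activity habits will be included". The parenthesis is the only definition of a change in eating. No test, level of testing (person or group), size of change or margin is attached to it.
- **Relevant concomitant care {11d}** gives the purpose, which is to isolate the effect of the intervention, and the means: "Participants will be asked to maintain the same behaviors throughout the study, then fill out the questionnaires midway and after the study to verify". Each person therefore supplies one questionnaire before, one midway and one after.
- **Methods to handle protocol non-adherence {20c}** repeats the condition as part of adherence: "no noticeable change in eating and physical activity habits, assessed by the Block questionnaires". It then says that, if non-adherence occurs, outcomes will be tested in an intention-to-treat set of all randomised participants and in a per-protocol set. That per-protocol set is defined by exercise completion alone.

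**The concern.** The rule treats the lack of a significant difference as the absence of a change. That creates two difficulties.

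First, the sentence selects participants, but a significance test needs an estimate of error, and a single participant with one value per occasion provides none. An analyst would have to invent a cut-off, possibly after seeing the data.

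Second, a group-level test could be run, but it cannot say which participant to leave out. Its non-significance also becomes more likely as the sample shrinks or the questionnaire gets noisier, so poorer data make stability easier to declare.

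Participants know their dose ({17a}), and ApoB, triglycerides, glucose, insulin and fat mass can plausibly respond to intake. A non-significant check is weak support for the attribution that {11d} seeks.

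**Working it through.** **The plan's own figures.** The protocol states no power or miss rate for the diet comparison, so there is none to reproduce. The one figure borrowed is 20 per arm, from Sample size {14}: "sample size calculation revealed a sample size of 60 subjects (20 per group". The inputs given there for ApoB ("Assuming a power of 0.90, *α* = 0.05, and an effect size of *d* = 0.80, a paired samples one-tailed *t*-test") lead to 15 by the noncentral t rather than 20. That is a separate matter, and 20 is taken here as the planned number.

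**Reading 1: one person.** A pre-post t-test on n differences has n − 1 degrees of freedom. With one difference per person, n − 1 = 0, so there is no standard error and no p-value. The midway questionnaire does not help: it is also a single value, and the spread across the three occasions is the very change being tested, so it cannot serve as the error as well.

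**Reading 2: a group.** Inputs and assumptions:

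- Alpha 0.05, from {20a}: "the significance level of all comparative data will be set as *p* ≤ .05". Sidedness is not stated there; two-sided is assumed.
- A paired t-test within each arm, which {20a} assigns to "pre- and post-measures of both primary and secondary physiological outcomes within each group", and between arms: "A one-way ANOVA will be used to compare the primary and secondary outcomes pre-post mean change between the three groups". Both are named for outcomes; their use for diet is an assumption.
- The true shift d is in units of the SD of individual change in intake. The protocol gives no such SD, so a range is shown.

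Formulas for the miss rate (1 − power):

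- Paired t, one arm: noncentral t with 19 df and noncentrality d√20. At d = 0.5 this is 0.5 × 4.472 = 2.236.
- ANOVA, 3 × 20, arm means 0, d/2 and d: noncentral F with 2 and 57 df and noncentrality 60 × d²/6 = 10d². At d = 0.5 this is 2.5.
- Paired t pooled over 60: noncentral t with 59 df and noncentrality d√60. At d = 0.5 this is 3.873.

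| True shift d | Missed, paired t in one arm (n = 20) | Missed, three-arm ANOVA | Missed, paired t pooled (n = 60) |
|---|---|---|---|
| 0.3 SD | 75% | 88% | 37% |
| 0.5 SD | 44% | 74% | 3% |
| 0.8 SD | 8% | 41% | < 0.1% |

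The pooled test is much more sensitive to a shift common to everyone, but it cannot show whether diet moved differently between doses, which is what matters for a dose comparison.

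**Precision available.** The 95% CI half-width for a mean change within an arm is t(0.975; 19)/√20 = 2.093/4.472 = 0.47 SD. For a difference between two arms it is t(0.975; 38) × √(2/20) = 2.024 × 0.316 = 0.64 SD.

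**The case against.** The strongest reply has four parts.

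- **The text filters persons, so group miss rates may not apply, and the tests used are ones the protocol names for outcomes.** This stands. The table shows what non-significance would be worth if someone ran the obvious group test; it does not describe a procedure in the plan. A reader might infer that the plan has a fixed 44% to 74% chance of missing a diet change, or about 92% per person. The documents do not support that. The first two figures need an assumed 0.5-SD shift, and the third also needs a ±1.96 SD individual cut-off that appears nowhere in the protocol.
- **The protocol never says a non-significant result proves that diet did not confound.** This also stands. {11d} speaks of verifying behaviour, and it asks participants to keep their habits and prohibits additional diet and exercise interventions. The point is that significance is a poor tool for that verification.
- **{20c} provides sets that do not use the diet rule.** True, and it limits the harm from selection. But those sets are triggered only if non-adherence occurs, which this rule helps to define, and neither set shows that diet was stable.
- **A numeric threshold is normally left to the analysis plan.** That would be an answer if {20a} were silent. It is not silent: it fixes significance as the criterion.

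A further caution is fair. Arms are randomised, so a later diet shift that differs by dose may be a consequence of the dose rather than a confounder.

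**Conclusion.** The criterion in {20a} is badly fixed. For an individual it cannot be carried out, and this needs no numerical assumption. For a group, non-significance does not establish stability: over shifts of 0.3 to 0.8 SD the miss rate runs from 75% down to 8% within an arm and from 88% down to 41% across arms. Those ranges assume 20 per arm, two-sided 0.05, evenly spaced arm means for the ANOVA, and tests borrowed from the outcome analysis. They are illustrations.

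The finding does not show that diet will shift or that the ApoB comparison will be biased. It shows that the planned check cannot give the reassurance asked of it. Whether excluding participants on post-randomisation behaviour is sound is a separate question.

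**What to change.** 1. In {20a}, remove statistical difference as the definition of a diet change. For the per-protocol set only, use a stated numeric change in energy intake and in macronutrient share, fixed before allocation codes are opened. Say whether a change in either one is enough.
2. Use the same criterion in {11d} and {20c}. At present {20c} counts diet in adherence but leaves it out of the per-protocol set; the two must agree.
3. Report mean change in energy, each macronutrient and non-study physical activity by arm, and the between-arm differences, with 95% CIs. Do not state that diet was stable on the strength of a non-significant test.
4. Label any ApoB model that includes change in intake as exploratory, because that change occurs after randomisation and may be part of the dose effect.

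The cost is a few sentences and one table, from questionnaires already planned. The drawback is candour about precision: with CI half-widths of about 0.47 SD within an arm and 0.64 SD between arms, the trial may be unable to claim that diet was stable.

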### Outcomes {12}

#### Primary outcomes

##### Blood analysis

Baseline and post-training blood analysis will be measured via venipuncture of the antecubital vein. Five milliliters of blood will be drawn for the lipoprotein metabolism profile (LMPP), 1 mL will be drawn for insulin, 1 mL will be drawn for glucose, 1 mL will be drawn for HbA1c, and 1 mL will be drawn for hematocrit. The LMPP consists of an ApoB count, Lp[a] count, and cholesterol and triglyceride content of each lipoprotein subclass (VLDL, LDL, HDL). Hematocrit is calculated to adjust for plasma volume changes applied to the cholesterol and triglyceride content measures. Glucose and insulin measures will be used to calculate insulin resistance (IR) using the homeostatic model assessment (HOMA) [83, 84]. For each variable, individual change from baseline will be calculated. Data will be aggregated as mean ± standard deviation (SD) for each dose group as well as for male and female subgroups with each dose groups. The mean change ± SD for each variable will be compared between the 3 dose groups and subgroups.

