#### Recruitment {15}

Participants will be recruited via advertisement flyers posted in the communities of Gunnison County, social media, word of mouth, employee email lists of WCU and GVH, local newspaper and magazine ads, churches, and through physician referral among the Gunnison County health care providers. To account for the logistical capacity of data collection, participants will be recruited in cohorts of 12 (randomized into intervention groups) where each cohort will complete the entire study before the next cohort begins. This will continue until 20 participants per intervention group have completed data collection.

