### Assignment of interventions: allocation

#### Sequence generation {16a}

After completion of baseline testing and adaptive period, participants will be randomly allocated to a HIFT dose group at a 1:1:1 ratio by computer-generated random numbers. This will be conducted by [name], one of the investigators uninvolved with participant recruitment, enrollment, assessments, and exercise training. Randomization will be blocked in cohorts and stratified by sex. The block size will be concealed by this investigator until the primary endpoints have been analyzed.

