### Methods for additional analyses {20b}

To explore whether the outcomes vary significantly between men and women, a secondary analysis will be performed for the stratification variable of sex.

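### The main comparison is a one-way ANOVA of change with baseline, sex and cohort left out of the model, and a normality test decides whether means or ranks are compared

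*Protocol article*

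**What the plan says.** **Between-group test.** Statistical methods {20a}: "A one-way ANOVA will be used to compare the primary and secondary outcomes pre-post mean change between the three groups". The scale is set under Outcomes, Blood analysis: "For each variable, individual change from baseline will be calculated".

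**Randomisation.** Sequence generation {16a}: "Randomization will be blocked in cohorts and stratified by sex". Recruitment {15} sets cohorts of 12 and adds that "each cohort will complete the entire study before the next cohort begins".

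**Use of those factors.** Methods for additional analyses {20b} says that "a secondary analysis will be performed for the stratification variable of sex". The outcome sections also describe results for male and female subgroups. No section uses cohort in an analysis.

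**Choice of test.** In {20a}, "normality will be assessed using a Kolmogorov-Smirnov test", and then: "If normality exists, parametric tests will be used, if normality does not exist, non-parametric tests will be used".

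**Missing outcomes.** Also in {20a}, "a linear-mixed model will be conducted instead of ANOVA as this test accounts for missing data". Section {20c} repeats the mixed model for ApoB and leaves imputation open.

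**The concern.** The protocol restricts its randomisation by sex and cohort and measures every primary outcome at baseline, then names a between-group model that uses none of the three as a covariate or factor. Two things follow.

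- Subtracting baseline fixes its coefficient at 1. When the baseline-to-post correlation is below 1, this leaves more residual variance than estimating the coefficient does. With about 20 people per arm, that is precision already paid for and not used.
- Stratifying and blocking spread sex and cohort evenly over the arms. If either affects the amount of change, its variance stays in the error term of a one-way ANOVA even though the design has removed it from the arm contrast. The standard error is then too large.

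The normality gate is a separate matter. It lets each outcome's data decide whether the reported comparison is of means or of ranks. A reader therefore cannot tell in advance what quantity will be estimated for ApoB or any other outcome, and the answer may differ between outcomes in one results table.

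**Working it through.** **The plan's own figure.** Sample size {14} gives 20 per group from a paired one-tailed t-test with d = 0.80, α = 0.05 and power 0.90. Those inputs return 14.8, so 15 per group, not 20; with 20 that test would have 96% power. The dropout step does reproduce: 20/0.95 = 21.05, rounded up to 22. The mismatch between a paired calculation and a between-group comparison is a separate matter. Only the ApoB inputs and the 20 per arm are used below.

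**Inputs**
- Baseline ApoB 129, SD 25 mg/dL, and a 15% reduction: Sample size {14}. 0.15 × 129 = 19.35 mg/dL; 19.35/25 = 0.774.
- 20 completers per arm: Sample size {14}.
- Baseline-to-post correlation r: not given. Assumed 0.3 to 0.9.
- Share of change variance due to sex and cohort: not given. Assumed sex 0 to 30%, cohort 0 to 10%.

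**1. Baseline as a covariate.** With equal SDs σ before and after training:
- variance of change = 2σ²(1 − r)
- ANCOVA residual variance = σ²(1 − r²)
- ratio = (1 − r²)/[2(1 − r)] = (1 + r)/2

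Power below is for a two-sided t-test of HIFT3 against HIFT1 at α = 0.05, 20 per arm, taking 19.35 mg/dL as the between-arm difference. The degree of freedom for the covariate is ignored.

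| r | Variance ratio | SD of change | ANCOVA SD | Power, change | Power, ANCOVA |
|---|---|---|---|---|---|
| 0.3 | 0.65 | 29.6 | 23.8 | 52% | 71% |
| 0.5 | 0.75 | 25.0 | 21.7 | 66% | 79% |
| 0.7 | 0.85 | 19.4 | 17.9 | 87% | 92% |
| 0.8 | 0.90 | 15.8 | 15.0 | 96% | 98% |
| 0.9 | 0.95 | 11.2 | 10.9 | about 100% | about 100% |

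If the stated d = 0.80 is instead read on the change scale, change-score power is 69% whatever r is. The ANCOVA effect size is then 0.80/√((1 + r)/2), and power becomes 86%, 81%, 76% and 72% at r = 0.3, 0.5, 0.7 and 0.9.

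**2. Sex and cohort as factors.** Simulation, 4,000 runs per scenario: 5 cohorts × 2 sexes × 3 arms × 2 people = 60, outcome on the change scale with total variance 1. The three-arm F test is taken with no effect, and with arm means 0, 0.4 and 0.8 SD.

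| Share due to sex / cohort | Null rejection, one-way | Null rejection, adjusted | Power, one-way | Power, adjusted |
|---|---|---|---|---|
| 0 / 0 | 5.1% | 5.0% | 59% | 59% |
| 10% / 5% | 2.9% | 5.1% | 58% | 66% |
| 20% / 10% | 1.4% | 4.9% | 59% | 76% |
| 30% / 10% | 0.6% | 4.7% | 57% | 80% |

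Where the factors matter, the unadjusted test rejects too rarely. Where they do not, adjustment costs nothing visible.

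**3. The normality gate.** Simulation with 20 per arm: Kolmogorov-Smirnov test with estimated mean and SD in each arm, and a switch from ANOVA to Kruskal-Wallis if any arm fails at 5%. Applying the gate arm by arm is an assumption; the article does not say. Type I error of the two-stage procedure was 5.3% for normal data, 5.2% for lognormal data and 4.6% for t with 3 degrees of freedom. With truly normal data it still switched in 14% of data sets, in line with 1 − 0.95³ = 14.3%.

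**The case against.** The best defence is that nothing here is invalid. Under randomisation, change-score ANOVA and ANCOVA both estimate the arm difference without bias, Trial design {8} calls the trial exploratory, and the efficiency gain rests on a correlation the article does not report. At r = 0.8 the gain is about one percentage point. The power figures also simplify. The 15% in Sample size {14} describes change within HIFT3, so using 19.35 mg/dL as a between-arm difference assumes no change in HIFT1, and the planned test is a three-arm F test with Bonferroni follow-up. All of that stands and limits the size of the point. It does not remove it: the same section says the sample will establish superiority of HIFT3 over HIFT1 on ApoB, and such a claim calls for one test fixed in advance that matches the randomisation.

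The article does not support several stronger readings that a reader might infer.

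- *Baseline and sex are ignored.* The change score subtracts baseline, and sex has its own secondary analysis. What is missing is either as a term in the main model. Change scores also remove stable differences in level between sexes and cohorts, so only effects on change matter.
- *False positives are inflated.* Omitting the stratifiers makes the test conservative, and the normality gate held type I error near 5%.
- *The mixed-model fallback changes the question.* In its standard pre/post form, the group-by-time term on complete data gives the same mean-change contrast as the ANOVA. It is triggered by missingness, not by outcome values.
- *The gate misses skewness that matters.* The ANOVA is run on change, and subtraction makes skewed outcomes more symmetric. For differences of lognormals (log-SD 0.5, r = 0.5 to 0.8, n = 20) the test detects non-normality in only about 17 to 20% of samples, but a miss then matters less.

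**Conclusion.** The point holds as one of efficiency and pre-specification, not of validity. The named model leaves out baseline as a covariate and both randomisation factors, and the reported contrast may be of means or of ranks depending on a pretest.

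The gain from baseline adjustment is a variance ratio of (1 + r)/2. In power for a 19.35 mg/dL difference, that is about 18 points at r = 0.3, 12 at 0.5, 5 at 0.7 and 1 at 0.8. These figures assume equal SDs of 25 before and after training and an unadjusted two-sided test. Any further gain from sex and cohort depends on shares of variance that are pure assumption; if those shares are zero, there is none.

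It does not follow that the trial is underpowered for this difference. That depends on r: change-score power is 52% at r = 0.3 but 96% at r = 0.8, and the article does not let one choose between them.

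**What to change.** In {20a}, replace the one-way ANOVA of change, for each continuous outcome, with one pre-specified model: post-training value on arm, baseline value, sex and cohort. This can be an ANCOVA or the equivalent mixed model. If the mixed model is chosen, use it whether or not outcomes are missing, so that missingness no longer decides the method, and word {20c} to match.

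Delete the Kolmogorov-Smirnov gate. Name a rank-based or log-scale analysis in advance as a sensitivity analysis.

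The cost is wording plus a few degrees of freedom. With five cohorts (60/12) it is 1 for baseline + 1 for sex + 4 for cohort = 6; a sixth cohort makes it 7. No extra data are needed.
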